## Background

Hepaticojejunostomies represent a common step during pancreatic and liver surgery including partial pancreatoduodenectomy, major liver resections, and bile duct resections. Overall, a hepaticojejunostomy is considered as a safe procedure with low rates of postoperative complications including a leakage rate of 2.3% to 5.6% [1, 2]. However, failure of this anastomosis leads to considerable consequences with a high risk of prolonged hospitalization and the need for interventional drainage or re-laparotomy, which is associated with high morbidity and mortality, even in high volume centers [3, 4]. Known risk factors for leakage are previous chemoradiation, preoperative biliary drainage, impaired liver synthesis capacity, malnutrition, obesity, and anastomosis at the level of hepatic duct bifurcation [1].

However, leakage of a hepaticojejunostomy could always be associated with the surgical technique used. There are especially two common techniques used for hepaticojejunostomy: the interrupted suture technique and the continuous suture technique. According to a current national survey in Germany 56% of the participating hospitals stated that they use both techniques for performing a hepaticojejunostomy depending on the surgical sites, while 40% of the hospitals adhere always to one of the mentioned two techniques. These results show a relevant heterogeneity of the techniques used among hospitals in Germany [5]. There is an ongoing debate between advocates of both techniques, who argue with universal use (also for small ducts) and a potentially lower stenosis rate for the interrupted suture technique and with a better sealing of the anastomosis and operative time saving for the continuous suture technique.

Despite the frequent necessity of hepaticojejunostomies in surgery and the relevant consequences for the patient with leakage, there are no randomized studies to compare the different surgical techniques. For this reason, the presented randomized controlled multicenter trial was initiated to assess whether there is a significant difference in the occurrence of anastomotic leakage between the two groups interrupted suture versus continuous suture technique for performance of a hepaticojejunostomy during pancreatoduodenectomy.

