### Statistical considerations and sample size calculation

Literature was systematically reviewed to identify all published data to this topic (see Supplementary Fig. 1). There were no randomized controlled trials and only one retrospective analysis from Japan, which compared the interrupted suture technique with the continuous suture technique in the setting of liver transplantations [11]. However, these data are not suitable for a meaningful sample size calculation, as the leakage rates of this reported trial come from a different setting and seem to be high compared to data derived mainly from hepaticojejunostomies only or as part of a pancreatoduodenectomy (5.6% using interrupted sutures [1] and 2.3% using both techniques [2], respectively).

Therefore, an adaptive sequential sample size design was chosen: The sample size per patient group was set exploratively at a group size of 50 patients. Total sample size was 100 patients. The prevalence of the primary endpoint in the 100 patients examined then forms the data basis for an adequate further sample size analysis and consequently for a sample size adjustment. To proceed the study with the then new calculated sample size, some criteria have to be met: First, the absolute difference in the primary endpoint must be at least 1% to justify clinical relevance of the study. Second, the calculated sample size per group should not exceed 1000 patients in order to be able to meaningfully end the study.

Due to the design with multiple testing an error correction will be performed in statistical analysis. Due to the lack of reliable data in the literature, this adaptive design offers the best opportunity to get meaningful data with adequate power.

Statistical analysis will be performed using SPSS software. An intention-to-treat and a per-protocol-analysis will be used for the analysis of the primary outcome. Comparisons of metric and ordinal data will be calculated with the Student *t*-test or Mann-Whitney *U* test. The chi-square test was used for categorical data. Statistical significance will be set at *p* < 0.05.

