## Trial status

Recruitment is ongoing (study protocol version 2.0). The first patient was enrolled in March 2020. Recruitment of the last patient is planned for March 2024.

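### With 50 patients per group the 1% relevance criterion excludes only ties, so the 1000-per-group cap decides alone, and the resulting go/no-go rule barely separates no effect from a large one

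*Protocol article*

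**What the plan says.** The rule is in the Protocol article, section Statistical considerations and sample size calculation. The first stage is fixed without a calculation: "The sample size per patient group was set exploratively at a group size of 50 patients. Total sample size was 100 patients". The recalculation then rests on what is seen: "The prevalence of the primary endpoint in the 100 patients examined then forms the data basis for an adequate further sample size analysis".

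Two conditions must both hold for the trial to go on. The first is that "the absolute difference in the primary endpoint must be at least 1% to justify clinical relevance of the study". The second is that "the calculated sample size per group should not exceed 1000 patients in order to be able to meaningfully end the study".

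The same section gives the only leak rates for a comparable setting: "5.6% using interrupted sutures [1] and 2.3% using both techniques [2], respectively". The Background cites the same range. Significance is set at p < 0.05 and categorical data are compared by chi-square test. Neither a numerical power nor the sidedness of the test is given.

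**The concern.** The protocol presents 1% as the threshold for clinical relevance. A threshold of that kind should separate differences worth pursuing from those that are not. Here it is applied to a difference observed in 50 patients per group, where about one to three leaks per arm are expected (50 × 2.3% = 1.15; 50 × 5.6% = 2.8). The observed difference is too coarse and too noisy to carry that decision.

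This rule alone determines whether the trial continues and how large it becomes. If it responds mainly to chance, the trial may stop when a worthwhile difference exists or continue when none does. The Discussion says that adjusting after 100 patients makes the sample size calculation considerably more accurate, and that claim depends on this rule. A reader who takes 1 point as the relevant difference should also know whether the permitted maximum could test it.

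**Working it through.** **Inputs from the protocol.** 50 per group at stage 1; observed difference of at least 1%; at most 1000 per group; cited leak rates 2.3% and 5.6%; 1:1 allocation; significance level 0.05; chi-square test.

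**Assumptions.** Two-sided test and 80% power, with variants below. The 1% condition is taken to apply to the observed stage-1 difference, which is how the text reads. Neither the 50 nor the 1000 is derived in the document, so there is no planned figure to reproduce.

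**Formula.** With m = (p1 + p2)/2, the size per group is

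n = [1.960·√(2m(1−m)) + 0.8416·√(p1(1−p1) + p2(1−p2))]² / (p1 − p2)², rounded up.

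**Step 1: what the 1% condition can exclude.** One leak in 50 is 2%. The possible observed differences are 0, 2, 4, … points. Nothing lies between 0 and 2, so any threshold above 0 and up to 2% gives the same decision. The condition fails only on a tie. A tie also gives no finite sample size, so the cap would stop the trial there anyway.

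**Step 2: what the cap does to the stage-1 counts.** For 1 versus 2 leaks (2% and 4%, m = 3%): (1.960 × 0.24125 + 0.8416 × 0.24083)² / 0.02² = 1,141.

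| Leaks (of 50 vs 50) | n per group | Decision |
|---|---|---|
| 0 vs 1 | 388 | go |
| 1 vs 2 | 1,141 | stop |
| 1 vs 3 | 376 | go |
| 2 vs 3 | 1,863 | stop |
| 2 vs 4 | 553 | go |
| 3 vs 4 | 2,554 | stop |

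From 0 versus 1, one further leak in the arm with one (0 versus 2, 192 per group) keeps the decision at go. One leak in each arm more (1 versus 2) turns it to stop, at the same observed difference of 2 points.

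**Step 3: how often both conditions are met.** Sum the product of the two binomial probabilities (50 per arm) over all pairs of unequal counts whose n is at most 1000.

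| True rates | Tie | Both conditions met |
|---|---|---|
| 2.3% vs 2.3% | 28.5% | 52% |
| 5.6% vs 5.6% | 17.7% | 52% |
| 2.3% vs 3.3% | 24.5% | 53% |
| 2.3% vs 5.6% | 15.2% | 63% |

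With the recalculation at 90% power these become 52%, 51%, 53% and 63%.

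**Step 4: a true 1-point difference against the cap.** For 2.3% versus 3.3% (m = 2.8%): (1.960 × 0.23331 + 0.8416 × 0.23320)² / 0.01² = 4,272.

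| True rates | n per group | Power at 1000 per group |
|---|---|---|
| 1.3% vs 2.3% | 2,774 | 39% |
| 2.3% vs 3.3% | 4,272 | 27% |
| 4.6% vs 5.6% | 7,597 | 17% |
| 5.6% vs 6.6% | 8,991 | 15% |

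The range 2,774 to 8,991 becomes 3,713 to 12,036 at 90% power, 2,971 to 9,190 with continuity correction, and 2,185 to 7,082 one-sided. All exceed 1000. A 1-point difference fits under the cap only when the lower rate is close to zero (0% versus 1% needs 780), which is below anything cited.

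**Step 5: what 1000 per group can detect.** Solving n = 1000 for the difference at 80% power: from 2.3%, about 1.5 points down or 2.3 up; from 5.6%, about 2.5 down or 3.2 up.

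**The case against.** A reader might infer that the 1% floor and the 1000 cap contradict each other. They do not. One is a floor on the observed difference and the other a ceiling on the calculated size, and many stage-1 results satisfy both. The two cited rates set against each other, 2.3% and 5.6%, need 546 per group and pass.

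A reader might also infer that the protocol promises power for a 1-point difference. It does not. 1% is a minimum for going on, and the recalculation uses the observed prevalence. Every go therefore rests on an observed difference of at least 2 points, with a continuation size often well below 1000. The cap is meant to stop the trial when the calculated size is too large. So Step 4 shows a limit that the protocol leaves unstated, not an error in a stated calculation.

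Nor can the recruitment end date under Trial status be projected onto 2,000 patients. The section Trial design and study setting says that one institution recruits so far and that further centres are planned, so a first-stage rate says little about a later one.

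Finally, the trial calls itself explorative, acknowledges the lack of comparative data, and appears here as a condensed article. The power and the recalculation formula may stand elsewhere, and their absence is not the point. The two conditions themselves are stated here with numbers, and what they do follows from those numbers and the first-stage size. That part of the concern stands.

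**Conclusion.** The concern holds as a weakness of the stated decision rule and should be fixed. At 50 per group the 1% condition adds nothing to the cap: it excludes ties and no other result. The rule as a whole lets the trial proceed with probability about 52% under no difference, 53% at a true 2.3% versus 3.3%, and 63% at a difference of 3.3 points. It hardly distinguishes these cases. Separately, a true difference of the size called clinically relevant could not be adequately powered within the cap at the cited rates (15% to 39% power at 1000 per group).

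The tie result needs only the stage-1 size and the reading that the condition applies to the observed difference; slightly unequal groups would not change it materially. The other figures assume 80% power and two-sided 0.05. The variants tried do not alter the conclusion. The error correction for multiple testing that the protocol announces would make the required sizes larger if it lowers the significance level.

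**What to change.** 1. Use the first 100 patients only to estimate the pooled leak rate. Calculate the sample size from that rate and a fixed planning difference chosen and justified on clinical grounds. Remove the filter on the observed difference.
2. State the power and sidedness used, and the difference that 1000 per group can detect. At 80% power and two-sided 0.05 this is about 1.5 points down or 2.3 up from 2.3%, and about 2.5 down or 3.2 up from 5.6%. These figures show what the cap allows; they do not define what is clinically relevant.
3. If 1 point remains the relevant difference, state that the trial cannot test it within the cap at the cited rates, and restate the aim as estimating the difference with a confidence interval.

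The cost is protocol wording, plus the work of justifying a planning difference. The stated detectable difference will look less favourable than 1%. The change is best made before leak counts by arm are examined.

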### Dissemination policy

After completion of the study, the results will be published in an international journal.

## Discussion

This clinical trial is one of the first randomized controlled study to investigate the safety and efficiency of two commonly applied suture techniques (the interrupted versus the continuous suture technique) in patients undergoing a hepaticojejunostomy during pancreatoduodenectomy. In addition to this study, there could be identified a second ongoing registered study on the same issue in China (ChiCTR1900020605).

Although the performance of a hepaticojejunostomy is a common procedure in hepato-pancreato-biliary surgery and a leakage of this anastomosis is associated with relevant morbidity and mortality, very few studies have dealt with this topic to date. A comparison of the suturing techniques with regard to the leakage rates was only carried out in one retrospective study in the setting of liver transplantations. This illustrates the necessity and usefulness of a study to compare the suturing techniques for hepaticojejunostomy during pancreatoduodenectomy.

Before initiating the present trial, a Germany-wide survey was carried out on the application of the various suturing techniques for hepaticojejunostomies. This confirmed that there is enormous heterogeneity in the technology used. While the majority use both techniques depending on the intraoperative situs, 40% of those questioned are rigidly attached to their technique. The bile duct diameter was cited as the most important decision criterion for those who use both techniques. This shows that very small bile ducts in particular can often be better treated using the interrupted suture technique. Therefore, the lower limit of the bile duct diameter in our study was set to 5 mm.

Due to the small amount of data comparing surgical techniques for hepaticojejunostomies, the sample size calculation is a particular challenge. There are only data available comparing the interrupted and the continuous suture technique in the liver transplant setting, where the risk of leakage is likely to be higher. Published data from the pancreatic surgery setting show lower leakage rates. However, in this pancreatic setting, there are no comparative data. To compensate for this lack of data, an adaptive design with an interim analysis after 100 patients was incorporated. At this point in time, the sample size can be adjusted, which significantly increases the accuracy of the sample size calculation.

In summary, we have emphasized the importance of the suture technique for hepaticojejunostomies, as hepaticojejunostomies are common procedures and a leakage of the hepaticojejunostomy is associated with relevant sequelae for the patients. In addition, the paucity of the available data was presented by performing a systematic literature review. Therefore, the initiation and implementation of this trial represents the logical step.

## Trial status

Recruitment is ongoing (study protocol version 2.0). The first patient was enrolled in March 2020. Recruitment of the last patient is planned for March 2024.

## Data Availability

We ensure that our datasets will be either deposited in publicly available repositories or presented in the main manuscript or additional supporting files.
